### **Sample size calculation**

To judge the adequacy of the intended samples sizes, we performed simulation studies using the estimated population means, the estimated populations standard deviations (recently published for COMP), and the estimated residual variance as true parameter values and assuming a correlation of 0.8 between intercept and slope. We then varied the population standard deviation of the slope by factors of 2 and 3 because we expect in our study a substantially larger population variation due to wider age range and including both diseased and healthy subjects. We conducted four simulation studies corresponding to the intended main analyses. All simulation studies are based on the planned sample size of 96 subjects and include 2500 repetitions per simulation.

With respect to *the primary objective*, the first simulation study looked at the standard error of the estimates of the population standard deviation of the slope. We observed standard errors of 1.87, 1.27, and 1.24 for population standard deviations of the slope of 3.7, 7.4 and 11.1, respectively. This suggests that we can obtain a rather precise picture of the population variation.

In the second simulation, we looked at the power to demonstrate a significant interaction between load and a single normally distributed covariate that can explain some of the biological variation of the slope. Already for a population standard deviation of 3.7, we obtained a power of 71% if the covariate can explain 50% of the biological variation. For a population standard deviation of 7.4, we reached a power of 85% if the covariate can explain at least 25% of the variation. For a population standard deviation of 11.1, we obtained a power of 89% if the covariate can explain at least 20% of the variation.

In the third simulation we considered the case of three normally distributed covariates with a correlation of 0.3, equal interaction terms with the load, and explaining together a certain percentage of the biological variation. We assumed here a moderate correlation of 0.3 to take into account that tissue status and inflammation status are both probably related to age and to each other. Our interest was the power to demonstrate a significant interaction with the load for one a priori selected covariate if the covariates together can indeed explain a large amount of a substantial population variation. For a population standard deviation of 7.4, we reached a power of 70% if the covariates explain together at least 82% of the variation, and for a population standard deviation of 11.1 we reach a power of 80% if they explain together 74% of the variation. This suggests that we will be able to demonstrate interactions between tissue status/inflammation status and ambulatory load on top of the interaction with age if the interactions are of similar magnitude as those for age, if all three factors explain a substantial amount of the biological variation, and if we have a substantial population variation of the slope.

With respect to the secondary objective, we can use standard formulas to determine the power to demonstrate a significant association in dependence on the true correlation between the individual slopes and a clinical outcome. They indicate that we have a power of 72% to find a significant association if the true correlation is 0.3, and a power of 95% if the true correlation is 0.4, taking into account a potential drop out rate of 10%. With respect to the ability of assessing an independent prognostic value, we performed a simulation study taking up the scenario of the third simulation study above, but now focusing on the situation where age, tissue status and inflammation can explain the variation in the individual slopes only to a smaller degree of 40%. If we further assume that these three variables together can explain the variation in the clinical outcome to the same degree as the individual slopes, we obtain a power of 80% to demonstrate an independent prognostic value if the individual slopes have a partial correlation of 0.6 with the outcome.

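### The 80% power for independent prognostic value is stated for 96 subjects, but the plan's own 10% drop-out allowance leaves about 86 at 24 months, where scaling suggests roughly 75%

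*Protocol*

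**What the plan says.** All of the power statements are in protocol section 4.1, under Sample size calculation.

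- On the number of simulations: "We conducted four simulation studies corresponding to the intended main analyses".
- On their size: "All simulation studies are based on the planned sample size of 96 subjects and include 2500 repetitions per simulation".
- Three simulations are then described for the primary objective: the precision of the slope's standard deviation, one covariate, and three covariates.
- For the secondary objective, standard formulas are used first: "we have a power of 72% to find a significant association if the true correlation is 0.3", followed by "a power of 95% if the true correlation is 0.4, taking into account a potential drop out rate of 10" per cent.
- For independent prognostic value the section returns to simulation: "we performed a simulation study taking up the scenario of the third simulation study above", now supposing that "age, tissue status and inflammation can explain the variation in the individual slopes only to a smaller degree of 40" per cent. The result is: "we obtain a power of 80% to demonstrate an independent prognostic value if the individual slopes have a partial correlation of 0.6 with the outcome".

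Two other places matter. Section 3.3 defines cartilage degeneration as the difference between baseline and the 24-month follow-up. Section 4.2 continues recruitment until each group of 24 has completed baseline and all three test days. It describes measures to limit later losses but no replacement of them.

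**The concern.** Two power statements for the same objective, one after the other, appear to rest on different numbers of subjects. The formula-based pair carries an explicit allowance for loss to follow-up. The simulated figure carries none and falls under a general statement of 96 subjects. Both concern outcomes that exist only for people who return at 24 months.

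The 80% is the only power figure for the second step of the secondary analysis, in which the individual slopes are adjusted for age and then for tissue status and inflammation. A reader would take it as the power of the planned analysis with the planned allowance for loss. On the text, it is the power with no loss at all.

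**Working it through.** **Inputs from the protocol.** Planned N = 4 × 24 = 96 (section 3.1). Potential drop-out 10%, powers 72% (r = 0.3) and 95% (r = 0.4), and 80% at partial correlation 0.6 with 2500 repetitions (Sample size calculation). Significance level 0.025 (section 4.1, stated for the joint look at five biomarkers). Two-sided testing is my inference, supported by step 2.

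**1. Evaluable number.** 96 × 0.9 = 86.4, so about 86.

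**2. Reproduce the neighbouring figures.** Fisher z: power = Φ(atanh(r)·√(n − 3) − z), with z = 2.2414 for two-sided 0.025.

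- n = 86, r = 0.3: 0.3095 × √83 − 2.2414 = 2.8199 − 2.2414 = 0.578, power 71.9%.
- n = 86, r = 0.4: 0.4236 × √83 − 2.2414 = 1.618, power 94.7%.
- n = 96, r = 0.3 and 0.4: 77.1% and 96.7%.
- n = 86 at two-sided 0.05: 80.5% and 97.1%.

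The printed 72% and 95% match n = 86 at two-sided 0.025. Drop-out was therefore deducted there.

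**3. Which simulation gives the 80%.** Four are counted and three are described for the primary objective. The only other simulation in the section is the one for independent prognostic value, so it is the fourth, and the statement about 96 subjects covers it.

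**4. Can the 80% be reproduced?** No. With error-free slopes, a partial correlation of 0.6 gives power above 99.9% at either n. The 80% must therefore reflect estimation error in the slopes, and the slope standard deviation and residual variance used in that run are not given. Working back from 80% at n = 96, the partial correlation of the outcome with the estimated slopes would be about 0.30 at level 0.025.

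**5. Scale the printed figure.** The noncentrality that gives 80% at n = 96 is 2.2414 + 0.8416 = 3.0830.

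| Method | Level | Power at n = 86 |
|---|---|---|
| √(86/96): 3.0830 × 0.9465 − 2.2414 = 0.677 | 0.025 | 75.1% |
| √(80/90), degrees of freedom with three covariates | 0.025 | 74.7% |
| Noncentral t | 0.025 | 74.9% |
| √(86/96): 2.8016 × 0.9465 − 1.9600 = 0.692 | 0.05 | 75.5% |

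**6. Cross-check by simulation under assumptions.** Three covariates correlated 0.3 explain 40% of slope variation, the partial correlation is 0.6, and the slopes are observed with an assumed reliability. At level 0.025, power falls from 92.7% (n = 96) to 88.9% (n = 86) at reliability 0.5, and from 74.9% to 70.0% at reliability 0.35. At level 0.05 and reliability 0.35 it falls from 83.1% to 77.3%. The loss is about 4 to 6 points. The level of power depends heavily on the assumed reliability.

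**The case against.** **The fourth run may have started from 96 and removed 10%.** The wording on 96 subjects does not strictly exclude this, and reconstruction cannot settle it. One attempt (slope standard deviation 7.4, error variance worked back from the precision figures in the first simulation) gave 83–84% at 96 and 78% at 86, so the printed 80% lies between the two. With 2500 repetitions the Monte Carlo standard error at 80% is √(0.8 × 0.2 / 2500) = 0.8 points. This objection stands as far as it goes: the case rests on what the section says, not on a recalculation. A silent deduction would still leave the general statement about 96 wrong for this run.

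**Nothing in the design depends on it.** The section sets no 80% target and accepts 70%, 71% and 72% elsewhere. That is correct and keeps the point modest. A reader might infer that enrolment should rise to 96/0.9 = 107, but the document does not support that.

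**It is not a central hypothesis.** Also correct. Hypotheses 2.1 to 2.3 concern correlations, whose power figures do allow for loss. Adjusted prognostic value is the second of five analysis steps, and it would be too strong to call it the main claim of the secondary objective.

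**Missing values are filled in, so 96 are analysed.** Section 4.2 does mention mean replacement and intent-to-treat analysis. Replacing a missing 24-month outcome by a mean adds no information about its relation to the slope and does not restore power.

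**Conclusion.** The point holds as an internal inconsistency. On the text, the 80% belongs to 96 subjects, while the plan's own allowance leaves about 86 for this analysis, and the adjacent figures already use the reduced number. Scaling puts the power near 75%, so the chance of missing the effect rises from 20% to about 25%.

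This rests on three things: that the statement about 96 subjects applies literally to the fourth simulation, that the 10% loss occurs, and that power scales with the square root of the number analysed. A reader might infer that the 80% is a proven calculation error, or that 75% is the true value. Neither is supported. The run cannot be reproduced from the document, and 75% is an approximation derived from the printed figure. Nor does the plan predict a 10% loss; it calls it potential.

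**What to change.** Re-run the fourth simulation with about 86 evaluable subjects. Print either the resulting power or the partial correlation that gives 80% at that number, and state the number used beside it, as is done for the formula-based figures. Limit the statement that all simulations use 96 subjects to the three for the primary objective. If the fourth run already removed 10%, keep the 80% and correct that statement instead. The approximate 75% should not be printed in place of a simulated result.

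The cost is one re-run of an existing simulation and a change to one or two sentences. Enrolment is unaffected, and the stated power is likely to become slightly less favourable.

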### **Subject characteristics**

To describe the characteristics of the subjects in each of the 4 subgroups descriptive statistic will be used. Mean and standard deviation of age, sex, body height, body mass, BMI, treatment (conservative or operative), time of operation (if applicable), time since injury, duration of physiotherapy, time of return to work, time of return to sport, or type of sports before injury will be calculated to describe the participating subjects. To monitor subjects for potential gait abnormalities the parameters from the gait analysis at baseline day will be used. In subjects with previous ACL injury (Group 2 and 4) method of treatment and time since injury will be recorded.

Parameters describing the walking stress test are mean walking speed, cadence, GRF, heart rate and gait kinematics and will be compared between loading conditions.

### **4.2. Handling of missing data**

All data will be checked for quality and completeness at the time of testing. Hence, we do not expect missing data due to technical difficulties. Blood samples will be taken at specific time points. Complicacy during blood sampling and delayed draw times will be registered in the study protocol. To minimize drop-out before completion of the 3 test days, we will inform the participants in detail about the duration and content of each session. To prevent logistical time problems, we will set all appointments prior to the clinical assessment. Incomplete data sets will be included in the statistical analysis. Missing values will be replaced by the mean. Recruitment will be continued until 24 participants per group completed the baseline assessment and all three walking stress test days to ensure complete data sets for addressing the primary objective.

To minimize the drop-out rate during the 24-month follow-up for answering the secondary objective, we will contact the participants at 12-months as intermediate clinical follow-up (KOOS only). We will account for drop-outs by performing intent to treat analyses.

## **5 REGULATORY ASPECTS AND SAFETY**

### **5.1 Local regulations / Declaration of Helsinki**

This research project will be conducted in accordance with the protocol, the Declaration of Helsinki, the principles of Good Clinical Practice, the Human Research Act (HRA) and the Human Research Ordinance (HRO) as well as other locally relevant regulations. The Project Leader acknowledges his responsibilities as both the Project Leader and the Sponsor.

### **5.2 Notification of safety and protective measures (HRO Art. 20)**

The project leader is promptly notified (within 24 hours) if immediate safety and protective measures have to be taken during the conduct of the research project. The Ethics Committee will be notified via BASEC of these measures and of the circumstances necessitating them within 7 days.

### **5.3 Serious events (HRO Art. 21)**

If a serious event occurs, the research project will be interrupted and the Ethics Committee notified on the circumstances via BASEC within 7 days according to HRO Art. 21.

### **5.4 Amendments**

Substantial changes to the project set-up, the protocol and relevant project documents will be submitted to the Ethics Committee for approval according to HRO Art. 18 before implementation. Exceptions are measures that have to be taken immediately in order to protect the participants.

### **5.5 End of project**

Upon project termination, the Ethics Committee will be notified within 90 days.

### **5.6 Insurance**

Not applicable. In the event of project-related damage or injuries, the liability of the University Hospital Basel provides compensation, except for claims that arise from misconduct or gross negligence.

## **6 FURTHER ASPECTS**

### **6.1 Overall ethical considerations**

The total time subjects invest in this study is about 22 hours. The majority of this time will be spent resting while sitting in a chair where subjects can read, study or do some office work. We will accommodate the participants weekly schedule and offer also offer testing sessions outside of regular working hours. By participating in this study, participants will receive feedback on their joint healthy and function that may be useful for their individual physical activity level. There are practically no risk factors in this study (see 6.2).

---

 A serious event is defined as any adverse event where it cannot be excluded, that the event is attributable to the sampling of biological material or the collection of health-related personal data, and which:

- a. requires inpatient treatment not envisaged in the protocol or extends a current hospital stay;
- b. results in permanent or significant incapacity or disability; or
- c. is life-threatening or results in death.

## 6.2 Risk-Benefit Assessment

This project is a risk category A project. Collecting health-related personal data in this study entail minimal risks and burdens for the patient. The physical stress during the walking stress test is comparable with walking with a backpack. The venipuncture will be carried out by a study nurse and is a standard clinical assessment with low infection risk. Double sided tape will be used to attach skin markers on specific anatomic landmarks. The tape may cause some skin irritation similar to a standard band-aid. This study provides no direct benefit to the patient. However, we will inform patients of their specific joint health and gait pattern measured in this study.

The risk of a MRI of the knee joint can be neglected. This standardized examination is performed in daily clinical practice. No contrast media will be given. Patients with pacemakers, neurostimulators or other conditional MR devices will be excluded. All female patients prior to menopause have to complete a pregnancy test before the MRI scan. If the test is positive, the patient will be excluded.

This study provides no direct benefit to the patient. However, subjects receive a summary of their joint health status and ambulatory gait function as appreciation.

## 7 QUALITY CONTROL AND DATA PROTECTION

### 7.1 Quality measures

All study personnel will be trained on all important project related aspects and be able to conduct quality control during and immediately after data collection. This is necessary to minimize missing data due to technical difficulties. Data quality will be checked weekly by the project leader. Internal audits will be carried out upon request by the host institution.

Blood samples will be analysed in duplicates and in random order. Differences due to inter-assay variation will be eliminated by comparing concentrations within subjects and testing all samples of any subject on the same plate. Intra-assay variability is estimated as coefficient of variation between the duplicates.

For quality assurance the Ethics Committee may visit the research sites. Direct access to the source data and all project related files and documents must be granted on such occasions.

### 7.2 Data recording and source data

All data will be entered into a master data file created in Redcap®. Electronic raw data will be stored on a backup drive that will be stored in a locked cabinet. All paper documentation (consent forms, questionnaires, CRFs) will be stored in a locked cabinet.

### 7.3 Confidentiality and coding

**Project data** will be handled with uttermost discretion and is only accessible to authorized personnel who require the data to fulfil their duties within the scope of the research project. On the CRFs and other project specific documents, participants will only be identified by a unique participant number.

Health-related personal data will be coded using a sequentially selected code from a predefined list of 6-digit codes containing letters and numbers. The code will only be broken if it is necessary to avert and immediate risk to the health of the person concerned or to guarantee the rights of the person. Participants will be asked if they are willing to be contacted in the future for subsequent follow-ups not currently planned in this study. The key to the code and participants' contact information will be kept in a locked cabinet and only accessible by the project leader.

**Biological material** in this project is coded by the unique participant code. Biological material will be appropriately stored in a restricted area only accessible to authorized personnel. When blood

samples are analysed by an external institution blood samples will be sent with an appropriate parcel service or are given directly to the company. The location of every blood sample is noted in the study log.

#### **7.4 Retention and destruction of study data and biological material**

The data obtained in this study will be used to establish a database. The data will be stored indefinitely. As specified above, the data will be coded and the identification key will be locked and only accessible by the project leader and project manager. Health related data will be stored for 10 years after publication of the research project.

When subjects have signed the informed consent blood samples will be stored indefinitely in a biobank and may be used for other studies. The samples may be reanalysed for additional markers as these become available and be used in potential future long-term follow-up studies. Should the biobank be terminated, the samples will be disposed as biological waste. As specified above, the data and biological samples will be coded, and the identification key will be locked and only accessible by the project leader and project manager.

### **8 FUNDING / PUBLICATION / DECLARATION OF INTEREST**

This study is mainly funded by the Swiss National Science Foundation (#320030\_184912). Some salaries of team members are covered by the Department of Orthopaedics and Traumatology of the University Hospital Basel. The SNSF is not involved in any aspect of the project.

Local progress reports will be used to disseminate information obtained in this study to healthcare professionals at our institution. The results of this study will be published at scientific conferences and in peer-reviewed international scientific journals. Any publications resulting from this project will only contain coded data, and establishing a direct link between health related data and the participants will be precluded.

Interested third parties may contact the project leader. Data will not be shared with third parties with lower data protection standards than CH or EU. Only coded data may be shared.

We declare no conflict of interest.

